### Study design

The study design is reported in line with the SPIRIT guidelines [44]. The experiment will take place in the EmpkinS laboratory in Erlangen, Germany. A repeated measures design will be used. Pain-free participants will execute standardized movement tasks with a mechanical low back-pain simulator (PainSim+) and without (PainSim-) a mechanical back-pain induction. An a priori computer-generated list based on random numbers created by one experimenter will be used to randomize the order of the conditions within each subject. S1 Fig provides an overview of the procedure of both phases.

### Eligibility Criteria

Participants are eligible for inclusion if they meet the following criteria:

1) Age between 18 and 65 years2) Sufficient knowledge of German (native speaker or C2 level)3) Body mass index (BMI) between ≥ 18 and ≤ 25 (due to the limited size range of the back pain simulator and Xsens suit, see below)4) Body height ≥ 155 cm (setup requirement for back pain simulator and Xsens suit)5) Good physical and mental health state (see exclusion criteria)

Exclusion criteria for participation are as follows:

1) Chronic back pain2) Depression (exceed cut-off score for clinically relevant depression symptoms of 22 on the General Depression Scale (German: Allgemeine Depressionsskala; ADS-L; [45])3) Serious diseases or conditions concerning the nervous system (e.g., severe epilepsy), musculoskeletal system (e.g., rheumatic arthritis), skin (e.g., acute neurodermatitis), and cardiopulmonary system (e.g., myocardial infarction); cancer, strokes; serious psychological disorders will be screened via the Web Screening Questionnaire for Common Mental Disorders (WSQ; [46])4) Acute infectious diseases (e.g., HIV/AIDS)5) Current pregnancy6) Acute herniation (e.g., spinal disc herniation)7) Acute back pain (ranging on a scale from 0 = *no pain* to 10 = *worst imaginable pain* between ≥ 5 and ≤ 10)8) Acute muscle and/or skeletal pain interfering with daily activities9) Diseases of the nerve roots and spine injuries10) Osteoporosis of the spine or back11) Surgery on or near the spine12) Diabetes mellitus (back pain simulator requirement, inter alia because of associated skin and soft tissue changes and higher risk of skin infections; e.g., [47])

We will follow an adaptive design and may change eligibility criteria for phase 2 based on the phase 1 findings.

### Sample size calculation and recruitment

We aim to examine 76 participants (phase 1: 20, phase 2: 56). The sample size for phase 1 follows recommendations for feasibility pilot studies, as the purpose of phase 1 is to test procedures for phase 2 [48,49].

Sample size calculations for phase 2 were based on a repeated measures design and calculated with G*Power. Based on similar study setups [27], we anticipate a medium effect size of approximately *d* = .40 [50] resulting in a total sample size of *N* = 51 (parameters: *d* = .40, alpha = .05, 1 – beta = .80). To compensate for dropouts and possible technical issues leading to missing data (especially motion capture data) we will recruit 10% additional participants, resulting in a total sample of *N* = 56.

Recruitment for both phases is carried out and monitored by the study team. Phase 1 is currently being conducted (from June 2025 until the anticipated completion at the end of November 2025), phase 2 is planned to begin in January 2026 and continue for eight months. Each participant will be offered a compensation of €20. Alternatively, participating students can receive course credits.

### Procedure

In phase 1 we aim to recruit primarily students via social media, flyers, university mailing lists, and word-of-mouth recommendation. For phase 2, recruitment will be expanded to the general population using the same strategies, supplemented by postings on public university websites and advertisements in local and regional media (e.g., newspapers).

The procedure is identical in both phases, except for the follow-up interview, which is only part of phase 1 and any small adjustments to maximize acceptability that may result from it. For a detailed overview of the participant timeline and measures see S2 Fig. In phase 2, we will additionally use a second motion capture technology (for more details see description below) to assess movement patterns. Each phase includes an online questionnaire for eligibility screening and baseline data and an on-site lab appointment. During the lab-session, participants complete two rounds of standardized movement tasks, once with and once without the back pain simulator. Throughout the session, stress levels (via saliva samples, cardiac measures, and self-report), self-reported pain, movement data (motion capture suit), and for female participants salivary progesterone and estradiol will be assessed. In phase 1, an acceptability and feasibility interview follows the lab session.

### Online Questionnaire

Prospective participants can register online (via link or QR code) and complete a questionnaire containing the consent to the screening questionnaire, demographic variables, presence of diseases potentially influencing outcomes (e.g., hypothyroidism), current medication intake (e.g., hormone preparations, psychotropic drugs), and for women questions regarding menstrual cycle and hormonal contraceptives, and the screening for inclusion and exclusion criteria. Demographic variables include age, sex, gender, occupational group, highest educational qualification, and ethnic affiliation. If participants are not eligible, they are informed about exclusion. If eligibility criteria are met, participants are asked to complete questionnaires assessing fear avoidance (Tampa Scale for Kinesiophobia for general population; [51]), fear avoidance response (Avoidance-Endurance Questionnaire; [52]), pain catastrophizing (Pain Catastrophizing Scale; [53]), coping with pain and pain-related distress (Fragebogen zur Emotionalen Schmerzverarbeitung; English: pain processing questionnaire; [54,55]), and stress perception (Perceived Stress Scale; [56]). After completing the questionnaire, potentially eligible participants are contacted via e-mail or phone, provided with information about informed consent, and offered a lab appointment on a business day between 11 am and 8 pm. In case of non-response, participants will be reminded once via email or phone and otherwise excluded.

### Lab appointment

Prior to the lab appointment participants will be informed via e-mail about the following instructions and restrictions: Waking up at least three hours before the appointment, no eating and caffein consumption one hour before the appointment, no smoking or exercise two hours before the appointment, and wearing comfortable clothes with thin fabric (no dresses or skirts). The lab appointment begins with the experimenters obtaining written informed consent. Participants then provide a baseline saliva sample for stress assessment (s0), which includes carefully moving a cotton roll (Salivette®, Sarstedt, Nümbrecht, Germany) in their mouth for 1.5 min. Afterwards, their body weight, height, and waist and hip circumference are measured. Female participants additionally provide a saliva sample of 5 ml via passive drooling (pooling saliva in the mouth and allowing it to drip into the sample tube) for the analysis of progesterone and estradiol levels as they might influence pain perception [57,58] and stress responses [35,59]. The core part of the experiment is conducted under two conditions in randomized order, namely, once with and once without the back pain simulator to allow for within-subject comparison. Before each condition, participants complete the Short Stress State questionnaire (SSSQ-G; [60]) and provide another saliva sample (s1). Participants then perform six movement tasks: five from the Back Performance Scale [61] and a sit-to-stand task (comparable to [62]; adjusted arm position: hands are placed relaxed on the legs). Movement quality is rated by an experimenter (see Additional File 1), and a video of the movement execution is recorded. Throughout the tasks, participants wear an inertial measurement unit (IMU)-based motion capture suit (Xsens MVN, Movella, Henderson USA; for more details see [63]). In phase 2, this will be supplemented by the EmpkinS holographic 6D wireless locating technique and integrated localizable electromyography radio transponders (EmpkinS sensor technology; [64,65]). After each task, participants rate pain intensity, emotional distress, and pain-related impairment on a visual analogue scale (VAS). Following task completion, the SSSQ-G and a third saliva sample (s2) are collected. The entire procedure is repeated under the alternate condition (with/ without low back pain simulator), including an SSSQ-G assessment before and after the six movement tasks, as well as another saliva sample (s3) after the movement tasks. In total, each participant completes 2x6 movement tasks, provides 4 saliva samples, and 2x2 SSSQ-G assessments.

At the end of the lab session in phase 1, participants are interviewed about the experimental procedure to obtain qualitative feedback on the quality of the simulated back pain and the overall acceptance of the back pain simulator and the motion capture suit (see Additional File 2). The experiment will be conducted by two trained experimenters. Standardization will be ensured throughout the procedure. To maintain protocol adherence, experimenters follow a detailed checklist during the lab session, which also includes comment sections for any deviations from the protocol. If participants abort during the study, they will be asked about the reason, and their data will be excluded from analyses.

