### Experimental procedure

#### Movement tasks (Back Performance Scale and Sit to Stand Task).

The Back Performance Scale (BPS) was developed to measure performance of mobility-related activity in back pain [61]. It comprises five tasks: the sock test, roll-up test, finger-floor, distance test, pick-up test, and lifting test (see Additional File 1). Performance regarding the participant’s effort and execution of the tasks is assessed by using a 4-point ordinal scale from 0 (best performance, e.g., “Can do the task with ease in varied ways”) to 3 (worst performance, e.g., “Cannot perform the task at all or need external support”) with individual wordings for scoring categories for each movement task [61]. In the lifting task, an additional specification is to put a time limit of one minute and count the repetitions of the participant. To ensure proper execution and not ambition, participants are not informed about this time limit beforehand. The whole BPS sum score ranges from 0 to 15 with lower scores indicating better performance and back mobility.

The sit-to-stand task (STST) was originally developed to measure performance of lower extremity muscles [66] and has also been used in the context of CBLBP [67]. The task comprises standing up from a chair and sitting down again, which will be repeated three times. For the current study, the performance rating was adapted to match the rating scale of the BPS, i.e., performance of mobility-related activity is rated from 0 to 3 (see Additional File 1).

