### Outcomes

#### Acceptability and feasibility (phase 1).

The main aim of phase 1 is to assess the feasibility and acceptability of various aspects of the study setup. Regarding feasibility, phase 1 will provide insights into the best way to integrate the various study components (the back pain simulator, the tasks and the measurement techniques) to identify changes in movement execution related to back pain. The results of the interview will provide information of the acceptability of the back pain simulator, the movement tasks, and the sensor technologies.

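### Excluding all data of participants who abort can select on the outcome and weaken the pain contrast, and it leaves aborters out of the phase 1 feasibility analysis

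*Protocol article*

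**What the plan says.** The rule stands at the end of the Lab appointment section: "If participants abort during the study, they will be asked about the reason, and their data will be excluded from analyses". It covers both phases and both conditions, any reason for stopping, and ratings already given before the stop.

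Other parts of the article bear on it:

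- **Back pain simulation.** Rivets press on the lower back to produce pain. Hypotheses 1 to 4 expect more pain, fear, impairment and stress in PainSim+.
- **Acceptability and feasibility (phase 1).** "The main aim of phase 1 is to assess the feasibility and acceptability of various aspects of the study setup". Acceptability comes from an interview held at the end of the lab session.
- **Movement tasks.** The observer scale already has a worst category, score 3, with the example wording "Cannot perform the task at all or need external support".
- **Sample size.** "we anticipate a medium effect size of approximately *d* = .40", with "alpha = .05, 1 – beta = .80", "resulting in a total sample size of *N* = 51". Then "we will recruit 10% additional participants, resulting in a total sample of *N* = 56", to cover dropouts and technical losses together.
- **Statistical methods.** Phase 2 is analysed by repeated-measures MANOVA or ANOVA. Multiple imputation is planned only if the data are missing completely at random.

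**The concern.** Aborting happens after exposure, and the exposure can cause it. Someone who stops because the simulator hurts too much is probably a person with a large difference between conditions. Removing that person, including every task and rating already completed, makes membership of the analysis set depend on the quantity being estimated.

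Two things are at stake. In phase 2, the within-person contrasts for hypotheses 1 to 4 could be too small and the tests weaker than planned. In phase 1, a person who could not finish is highly informative about acceptability, may never reach the closing interview, and is excluded by rule. Phase 1 findings may change the phase 2 eligibility criteria and procedure, so what is left out there carries forward.

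**Working it through.** **1. The plan's own figure.** Inputs from the sample size section: d = .40, alpha .05, power .80. For a paired t-test with two-sided alpha, power comes from the noncentral t with n − 1 degrees of freedom and noncentrality d√n.

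- n = 51: power .7999; n = 52: .8078. The stated 51 reproduces as a two-sided calculation. Sidedness is not stated; a one-sided test would need only about 41.
- 51 × 1.10 = 56.1, so the stated 56 reproduces.

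The sample size is not the problem.

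**2. What the rule does under selective aborting.** Assumptions, not given in the article:

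- The within-person difference D is normal with mean .40 and SD 1, so d = .40.
- A fraction q aborts: those highest on a latent tendency to abort that correlates ρ with D.
- 56 are recruited, and the number left is 56 × (1 − q), rounded.

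With a the (1 − q) normal quantile and λ = φ(a)/(1 − q), the people who remain have

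- mean = .40 − ρλ
- variance = 1 − ρ²(aλ + λ²)
- d = mean / √variance

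For q = .10: a = 1.2816, φ(a) = .1755, λ = .1755/.90 = .195, and aλ + λ² = .250 + .038 = .288. The number left is 56 × .90 = 50.4, taken as 50.

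| ρ | mean | SD | d | power, n = 50 |
|---|---|---|---|---|
| 0 | .400 | 1.000 | .40 | .79 |
| .3 | .342 | .987 | .35 | .67 |
| .5 | .303 | .963 | .31 | .59 |
| 1 (upper bound) | .205 | .844 | .24 | .39 |

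At ρ = 1 the raw mean falls by 49% (.205/.400 = .51). The standardised effect, which drives power, falls by 39% (.243/.40 = .61), because truncation also shrinks the SD.

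**3. Other abort rates, ρ from .3 to .5.**

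- 5% aborting (n = 53): d .37 to .35, power .75 to .72.
- 20% aborting (n = 45): d .30 to .24, power .51 to .35.

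A separate simulation of the same model agrees to within .01 on d and power.

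**4. The over-recruitment.** With 10% aborting and ρ = 0, power is .79, so the allowance does its job. With ρ above 0 the shortfall comes from the smaller d, and extra participants recruited under the same rule are selected in the same way.

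**5. Phase 1, side by side.** The main aim is feasibility and acceptability. Abort reasons are asked and deviations are noted on a checklist. The rule then takes aborters' data out of analyses, and the article does not name aborts among the feasibility outcomes.

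**The case against.** The strongest reply is that selective aborting is assumed, not shown. The article gives no abort rate, timing or reasons. Stops for illness, time or suit discomfort, or in PainSim-, need not attenuate anything. The belt's tightness is adjustable. A person who cannot do a task but continues stays in with a score of 3. Small adjustments for acceptability may follow phase 1, before any hypothesis is tested. All of this stands, which is why the conclusion is conditional. A reader might infer that the rule certainly biases the effect towards zero; the document does not support that.

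The size is also open to challenge. A correlation of 1 cannot hold for pain, fear, mobility, HRV and stress at once. If the true pain effect were much larger, say d = 1.0 (an assumption), the same formula with 10% aborting gives about .95 at ρ = 1 and .94 at ρ = .5, with negligible loss of power. This stands too: the illustration matters for outcomes near the planned .40.

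Two stronger readings are tempting and fail. One is that the rule contradicts the missing-data plan. It does not: imputation there depends on data being missing completely at random, and pain-driven aborts would not meet that condition. Excluding aborters and imputing sporadic gaps can coexist. The other is that the rule hides non-feasibility. Reasons are asked, deviations are recorded, nothing says the count goes unreported, and there is no completion-rate endpoint to distort.

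Finally, deleting the sentence would not suffice. Someone who stops in a first-position PainSim+ round has no PainSim- data, so a complete-pair ANOVA or MANOVA could not use them. That is correct, and it affects the cost of the fix.

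What the reply does not remove is the rule itself. It is stated, without exceptions, and keyed to an event the tested condition can cause.

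**Conclusion.** The point holds in conditional form and should be fixed. The blanket exclusion can select on the outcome, and it attenuates the condition contrast whenever aborting is positively related to the individual pain effect. With d = .40 and 10% aborting, moderate correlations of .3 to .5 bring d to about .35 to .31 and power to about .67 to .59. At 5% aborting the loss is modest, and at zero correlation there is no bias. These figures rest on an assumed abort rate, an assumed correlation and a normal model. No size is claimed for the exploratory fear-avoidance associations, which were not calculated.

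For phase 1 the conclusion needs no arithmetic: participants who stop are left out of the analysis of a study part whose main aim is feasibility and acceptability, and no use of their reasons is planned in the article.

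**What to change.** Replace the exclusion sentence with a rule along these lines:

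- Keep every observation collected before the abort, subject to consent, for everyone who started the first condition.
- Analyse these data with a method that accepts partial records, either a mixed model or multiple imputation under missing at random, in place of or alongside the complete-pair ANOVA/MANOVA.
- Retain the existing observer score of 3 for a task that was stopped because it could not be performed.
- Give a completers-only analysis and a not-at-random scenario as sensitivity analyses.
- Report the number, condition, timing and reason of aborts, as a feasibility result in phase 1 and with the main results in phase 2.

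No new data collection is needed: partial records arise in any case, and the reasons are already asked. The cost is more than rewording, because the present plan contains no mixed model and the analysis method must be extended. Missing-at-random methods only partly address pain-dependent aborts, which is why the not-at-random scenario is needed. The change is best made before the phase 2 data are analysed.

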### Experimental procedure

#### Movement tasks (Back Performance Scale and Sit to Stand Task).

The Back Performance Scale (BPS) was developed to measure performance of mobility-related activity in back pain [61]. It comprises five tasks: the sock test, roll-up test, finger-floor, distance test, pick-up test, and lifting test (see Additional File 1). Performance regarding the participant’s effort and execution of the tasks is assessed by using a 4-point ordinal scale from 0 (best performance, e.g., “Can do the task with ease in varied ways”) to 3 (worst performance, e.g., “Cannot perform the task at all or need external support”) with individual wordings for scoring categories for each movement task [61]. In the lifting task, an additional specification is to put a time limit of one minute and count the repetitions of the participant. To ensure proper execution and not ambition, participants are not informed about this time limit beforehand. The whole BPS sum score ranges from 0 to 15 with lower scores indicating better performance and back mobility.

The sit-to-stand task (STST) was originally developed to measure performance of lower extremity muscles [66] and has also been used in the context of CBLBP [67]. The task comprises standing up from a chair and sitting down again, which will be repeated three times. For the current study, the performance rating was adapted to match the rating scale of the BPS, i.e., performance of mobility-related activity is rated from 0 to 3 (see Additional File 1).

#### Back pain simulation.

To induce lower back pain, a back pain simulator from Produkt + Projekt Wolfgang Moll (Niederstotzingen, Germany) is employed [68]. The back pain simulator is a standalone component of an age simulation suit, the GERonTologic simulator (GERT). It consists of a black vest resembling a motorcycle back protector (see S3 Fig), that uses six large spike rivets (three on each side next to the spine) to simulate mechanical “stabbing” pain in the lower back. The vest is secured with two shoulder straps and a Velcro waist belt that allows adjustment of its tightness, and, consequently, pain intensity. To our knowledge, this back pain simulator is the only mechanical device designed to replicate lower back pain. Initial results indicate that wearing the age simulation suit leads to a decrease in functional and physical performance of young and older adults across various tasks requiring both gross and fine motor skills [69,70]. A preliminary test with the back pain simulator on a small sample revealed similar behavioral adaptations during the BPS movement tasks. Participants tended to stiffen and straighten their backs while moving and often bent the knees rather than their backs to pick up objects.

#### Motion capture technologies.

All movements tasks are recorded with an IMU-based motion capture suit (Xsens MVN, Movella, Henderson, USA). It consists of 17 sensor nodes attached to the body with Velcro straps, recording 6D IMU data (3D acceleration and 3D angular velocity) of the whole body with a sampling rate of 60 Hz. It is widely used for motion capture in research due to its portability and reliable kinematic data output [71,72]. In previous work, it has also been successfully employed to assess the influence of acute psychosocial stress induction on full-body movements [73,74]. After attaching the sensor nodes and obtaining relevant body measures (i.e., body height, shoulder width, arm span), the system is calibrated using a standardized procedure (see [74]). The raw IMU data is wirelessly transferred to a computer running the Xsens MVN Awinda software, which processes the data through a biomechanical model, ultimately providing time-series movement information from 23 body segments with 6 different channels and joint rotation angles from 22 joints. From these movement data, we will compute a set of features that is intended to characterize the specific movements performed during the experiment, and, especially, the effect of the back pain simulator on the movement execution.

In phase 2, movements will additionally be recorded using the holographic 6D wireless locating and motion tracking system (EmpkinS H6D-Tracking), developed within the EmpkinS Collaborative Research Center [65]. The Xsens suit will then serve as a reference system for the EmpkinS H6D-Tracking. The EmpkinS system consists of wearable radio transponders – referred to as EmpkinS Beacons – that can be localized by radar base stations. Each EmpkinS Beacon additionally includes an IMU unit to record 3D acceleration and 3D angular velocity as well as an analogue frontend with electrodes to record surface electromyography (sEMG) of the muscles under the skin area the Beacons are attached to [64].

